## **2.6 Summary of Literature Findings**

The literature review aims to comprehensively explore the pathophysiology of knee osteoarthritis (KOA), its prevalence, and the subsequent impact on both physical and psychological health. It encompasses an in-depth examination of the mechanism, prevalence, and consequences of KOA, leading to a discussion on current management strategies and a focus on laser therapy as an alternative approach. The review delves into the principles of laser therapy, evaluating clinical evidence regarding its effects on pain, physical function, and psychological health. Notably, it concludes by summarizing key findings and emphasizing existing knowledge gaps, providing a foundation for future studies. The subsequent sections detail the pathophysiology of KOA, its prevalence and impact, current management approaches, the mechanism of High-Intensity Laser Therapy (HILT), and clinical evidence of HILT in KOA.

The review recognizes the interconnectedness of physical and mental well-being in the context of KOA, emphasizing the multifaceted challenge it poses and the necessity for a comprehensive management strategy. It further underscores the potential of HILT as a promising therapeutic option for addressing KOA, calling for more integrated and extended-duration studies to elucidate its full therapeutic potential. Additionally, it addresses the lack of qualitative research on laser therapy, citing a study by undergraduate Dentistry students exploring the application of diode laser in frenectomy surgeries and providing evidence supporting its efficacy in reducing pain and facilitating healing.

### **3.0 Methodology**

The proposed study will consist of 3 phases:

- Phase 1: Quantitative design- Randomized Controlled Trial (Short and long-term outcomes)
- Phase 2: Qualitative study- Structured one-on-one interviews (Participants' experiences and perspectives)

### **3.1 Phase 1: Quantitative Design-Randomized Controlled Trial (Short-term Outcomes)**

#### **3.1.1 Study Design**

This prospective investigation will adopt a parallel-group, randomized, double-blinded (for both subjects and outcomes assessor), and placebo-controlled trial design. The study protocol adheres to the guidelines outlined in the Consolidated Standards of Reporting Trials (CONSORT). Participants will be randomly assigned to either the High-Intensity Laser Therapy with exercise (HILT+E; n = 20) group or the placebo laser with exercise (PL+E; n = 20) group.

#### **3.1.2 Study Settings**

The research will take place at Hospital Canselor Tuanku Muhriz UKM, Malaysia, where adults in the early stages of Knee Osteoarthritis (KOA) will undergo screening and recruitment from the Physiotherapy Department, ensuring they meet the specified inclusion and exclusion criteria.

#### **3.1.3 Target Population**

The intended participants for this research will be adults aged 18 years and older who are in the early stages of Knee Osteoarthritis (KOA). The inclusive and exclusive criteria will encompass:

##### ***3.1.3.1 Inclusion Criteria***

- i. Adults aged 18 years and above of both sexes.
- ii. Individuals diagnosed with unilateral or bilateral KOA by an orthopaedic doctor.
- iii. Those with a Kellgren-Lawrence classification of grade  $\leq 2$  (mild) based on a knee radiograph conducted within the last six months

- iv. Individuals capable of engaging in the intervention and assessment program without restrictions. In cases where both knee joints are affected, the knee with more severe symptoms, based on the pain score, will be included. If symptoms are identical in both knees, the dominant knee will be assessed.
- v. Individuals who can understand and express themselves in English and Bahasa Malaysia.

#### ***3.1.3.2 Exclusion criteria***

- i. Presence of other pathological conditions like rheumatic disease, prior hip or knee joint replacement, congenital dysplasia, osteochondritis dissecans, intra-articular fractures, septic arthritis, ligament or meniscus injury, and any other condition impeding the healing process, including diabetes mellitus and peripheral vascular disease
- ii. comorbidities hindering physical evaluation
- iii. ongoing participation in another KOA-related interventional study
- iv. individuals taking prescription glucosamine sulfate, which might potentially affect the study's outcomes.
- v. Participants who had undergone intra-articular knee injections (e.g., corticosteroid, hyaluronic acid, or blood-derived products) for KOA management in the last six months
- vi. Individuals who unable to understand and express themselves in English and Bahasa Malaysia.

#### **3.1.4 Sample Size Calculation**

The determination of the sample size for this study will be conducted using G\*Power software version 3.1.9.7, relying on a minimal clinically important difference (MCID) of 11 points for the primary outcome, Knee Injury and Osteoarthritis Outcome Score (KOOS), as indicated by (Eckhard, Munir et al. 2021). We will consider a pre-specified power of 90%, an effect size of 0.3, an alpha level of 5%, and a potential dropout rate of 20%, following the approach outlined by (Serdar, Cihan et al. 2021). Consequently, the necessary total sample size will be 40, with an allocation of 20 participants to each group.

#### **3.1.5 Sampling and randomization**

The screening, recruitment, and randomization (group allocation) of participants will be carried out by a researcher uninvolved in the intervention or outcomes assessment. After

recruiting 40 participants, they will be randomly assigned in a 1:1 ratio to one of two intervention groups using a computer-generated table and a simple block randomization method: (i) Group HILT with exercise (HILT+E; n = 20) and (ii) Group placebo laser with exercise (PL+E; n = 20). This randomization process will occur subsequent to participants receiving both verbal and written information about the study protocol and signing the written informed consent form.

### **3.1.6 Group allocation and intervention**

In this research, participants will be randomly assigned into one of two groups:

- Group 1 (HILT+E): Participants from this group will undergo individually tailored standard physiotherapy alongside high-intensity laser therapy for twelve weekly sessions. The treatment session will be administered by a qualified physiotherapist who has undergone training in prescribing laser therapy.
- Group 2 (PL+E): Participants will receive individually tailored standard physiotherapy with a placebo/sham intervention once a week for twelve sessions.

Participants in both Group HILT+E and Group PL+E will receive HILT (BTL-6000: 5 W, 1064 nm, 19 to 150 J/cm^2, and 3190 J per session) and sham laser (without emission of energy) as an adjunctive treatment, respectively, in addition to knee rehabilitation exercise (standard physiotherapy care). The specifics of laser interventions based on group allocation are outlined in the attached Appendix, with parameters and procedures derived from manufacturer guidelines (BTL-Corporate, 2020) and previous studies (Kheshie et al., 2014; Ahmad Nazari et al., 2019). To ensure participant blinding regarding their laser intervention, the laser procedures will be identical between groups, including visual light and acoustic indicators (de Paiva et al., 2019). Despite laser therapy being generally safe with few reported adverse effects (Rayegani et al., 2017), this study will implement specific safety measures and precautions. Participants will be required to wear special protective eyewear during laser application, and they will be periodically checked for any discomfort or overheating. Additionally, participants will be asked to report any adverse effects of the laser intervention during the weekly follow-up session.

Qualified physiotherapists from the Hospital Canselor Tuanku Muhriz UKM, unaware of the participants' laser grouping, will administer the personalized physiotherapy treatment,

adhering to recommended KOA treatment guidelines. The knee rehabilitation exercises utilized will be adapted from pertinent previous studies (Gay et al., 2016; Suzuki et al., 2019) and the recommended KOA treatment guidelines (Bannuru et al., 2019; Collins et al., 2019). Each session is anticipated to last one hour, encompassing various knee exercises. The exercise prescription and progression will be modified accordingly based on the individual patient's KOA. The examples of exercise components are:

- Range of motion
  - Prone knee bend (2 set, 10 repetitions each)
  - Supine alternate knee bend (2 set, 10 repetitions each)
- Stretching
  - Standing quadriceps stretch (1 set, 3-5 repetitions, 15 second hold each)
  - Calf stretch in long sitting (1 set, 3-5 repetitions, 15 second hold each)
  - Supine hamstring stretch (1 set, 3-5 repetitions, 15 second hold each)
- Strengthening
  - Sitting knee extension (Week 1-2: 1 set, 5 repetitions, 5-second hold; Week 3-5: 1 set, 7-10 repetitions, 5-10-second hold; Week 6-8: 2 sets, 10 repetitions, 10-second hold)
  - Supine straight leg raise (Week 1-2: 1 set, 5 repetitions, 5-second hold; Week 3-5: 1 set, 7-10 repetitions, 5-10-second hold; Week 6-8: 2 sets, 10 repetitions, 10-second hold)
  - Static quadriceps (Week 1-2: 1 set, 5 repetitions, 5-second hold; Week 3-5: 1 set, 7-10 repetitions, 5-10-second hold; Week 6-8: 2 sets, 10 repetitions, 10-second hold)
  - Side-lying straight leg raise (Week 1-2: 1 set, 5 repetitions, 5-second hold; Week 3-5: 1 set, 7-10 repetitions, 5-10-second hold; Week 6-8: 2 sets, 10 repetitions, 10-second hold)
- Functional Training
  - Sit-to-stand (10 repetitions)
  - Standing mini squat (10 repetitions)
  - Walking exercise (Approximately 2 minutes for each item)

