## **Executive Summary**

Knee osteoarthritis (KOA) is a prevalent chronic condition globally, contributing to knee pain and disability. Recent studies suggest that high-intensity laser therapy (HILT) holds promise as a treatment for KOA. However, clinical evidence supporting its efficacy, particularly over the long term, remains insufficient. This study aims to (i) assess the short- and long-term effects of HILT as a supplement to rehabilitative activities for individuals with mild to moderate KOA, focusing on joint morphologic changes, and (ii) explore the experiences and perceptions of individuals undergoing this combined intervention. The study will employ both quantitative and qualitative methodologies. The first phase of the study will be a randomized double-blinded controlled trial, which will involve 40 participants with mild-to-moderate KOA based on the Kellgren-Lawrence classification. Participants will be randomly assigned to either the HILT with exercise (HILT+E; n=20) or the placebo laser with exercise group (PL+E; n=20). For eight consecutive weeks, both groups will receive their prescribed laser treatment—HILT (5 W, 1064 nm, 19 to 150 J/cm^2, and 3190 J each session) or a placebo—along with KOA rehabilitation exercises once a week. Examples of KOA rehabilitation exercises are range of motion, stretching, strengthening, and functional training exercises. The exercise prescription will be modified based on the individual's progression. The outcome measures included are knee X-ray (cartilage thickness and joint space), Knee Injury and Osteoarthritis Outcome Score (KOOS), Timed Up and Go (TUG) test, and Numeric Pain Rating Scale (NPRS), which will be evaluated at three different time points by a blinded assessor: baseline, post-intervention, and follow-up after three months of the last session. Knee X-rays (to evaluate cartilage thickness and joint space) will be taken at baseline and follow-up. Two-way repeated measures ANOVA will be used to assess the effects of time, group, and the interaction between the two groups. In the second phase of the study, structured one-to-one interviews will be carried out with participants to explore patient experiences. Each interview will be audio or video-recorded with participants' consent, and questions will be posed in a conversational manner to capture both verbal responses and non-verbal cues. The qualitative data will undergo thematic analysis using ATLAS.ti software programs. The findings of this study are pivotal for deepening our understanding of the impacts of HILT and establishing an effective treatment regimen for KOA. These insights have the potential to improve the pathological condition, providing optimism for mitigating KOA progression.

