## 1.0 Introduction

### 1.1 Study background

Knee osteoarthritis (OA) is a common cause of knee pain worldwide, which is caused by repetitive stress and mechanical trauma leading to an inflammatory process within the knee joint, resulting in articular cartilage deterioration and loss of chondrocytes (Geng, Li et al. 2023). The primary method of dealing with musculoskeletal pain involves conservative techniques that include both pharmaceutical and nonpharmacological therapies. Recent research has demonstrated the effectiveness of nonpharmacological interventions, including exercise, heat modalities, and manual therapy (Soares Fonseca, Pereira Silva et al. 2023). Despite the guidelines for treating knee OA prescribe workouts on land or in the water, weight loss, and the use of a cane, alternatives are investigated for pain reduction, including topical NSAIDs, intraarticular corticosteroid injections, and physical modalities like laser therapy. High-intensity laser therapy (HILT), distinguished from low-level laser therapy (LLLT) by its greater output power, has shown positive effects on pain relief, range of motion, and functional improvement in knee OA (Siriratna, Ratanasutiranont et al. 2022). However, the lack of a standardized treatment protocol for HILT and significant variation in study outcomes highlight the need for further research in this area. This study aims to investigate the short-and long-term effects of high-intensity laser therapy combined with rehabilitation exercise on knee pain in adults with early knee osteoarthritis. The study also attempts to evaluate the long-term effects of high-intensity laser therapy combined with rehabilitation exercise on physical function and knee-related disability in adults with early knee osteoarthritis. Additionally, by combining high-intensity laser therapy with rehabilitation exercises, the study aims to investigate the potential disease-modifying effects of the treatment. Specifically, it focuses on how the treatment affects the structural aspects of the knee joint in adults with early-stage osteoarthritis. The study will be carried out using quantitative and qualitative approaches in a parallel-group, randomised, double-blind (subjects and outcomes assessor), placebo-controlled trial design. There will be three stages of it. Phase 1 involves a random allocation of 40 individuals to participate in one of two groups: 20 individuals in group 1 will be treated with high intensity laser treatment with exercise (HILT+E;  $n = 20$ ), while another 20 participants in group 2 will receive exercise and a placebo laser (PL+E;  $n = 20$ ). Each group is scheduled for weekly 60-minute sessions for eight weeks in consecutive weeks. However, phase 2 of the study extends an 12-week follow-up period to investigate the long-term effects of high intensity laser therapy in comparison to placebo laser therapy and exercise. All 40 participants from both groups are

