### **3.2 Phase 2: Qualitative Study-Structured One-On-One Interviews (Participants' Psychological Well-being, Experiences, and Perspectives)**

During the third phase of our research, we aim to qualitatively investigate the perspectives and experiences of adults with KOA who have undergone a 12-week intervention involving HILT with exercise, in comparison to those who received placebo laser therapy with exercise.

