### 3.2.3 Outcomes Measures

The outcomes of interest include participants' psychological well-being, experiences, and perspectives throughout the 12-week intervention involving HILT with exercise or placebo laser therapy with exercise. These outcomes will be explored through structured one-on-one interview, which allowing participants to share their subjective experiences and perceptions. The interview script is generated based on WHO-5 Well-Being Index and SF-36.

1. WHO-5 Well-Being Index: Developed by the World Health Organization, this index assesses overall psychological well-being by querying mood, vitality, and general well-being. The WHO-5 demonstrates strong internal consistency (Cronbach's alpha coefficient of 0.858) and convergent validity where the significant correlations with PHQ-9, HADS-anxiety, and HADS-depression (Maroufizadeh et al., 2019). Please refer to the Appendix 2.
2. Short Form 36 Health Survey (SF-36): Widely used to assess health-related quality of life, SF-36 provides valuable insights into psychological well-being. Despite being primarily designed for health-related quality of life, SF-36's total scores exhibit high responsiveness ( $>0.9$  effect sizes) (Clement et al., 2022). Thresholds of  $\leq 52$  in the MH subscale and  $\leq 56$  in the SF-36 effectively detect anxiety and depression, with additional reliable thresholds ( $\leq 35$  and  $\leq 40$  in MCS scores) for identifying these conditions (Matcham et al., 2016). Please refer to the Appendix 3.

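### Section 3.1.6 prescribes twelve weekly sessions where most of the protocol says eight, and the week labels of the two post-baseline visits cannot both be right

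*Protocol*

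**What the plan says.** Twelve sessions or weeks:

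- Section 3.1.6, laser arm: "Participants from this group will undergo individually tailored standard physiotherapy alongside high-intensity laser therapy for twelve weekly sessions".
- Section 3.1.6, sham arm: "Participants will receive individually tailored standard physiotherapy with a placebo/sham intervention once a week for twelve sessions".
- Section 3.2 describes interviewees as "adults with KOA who have undergone a 12-week intervention involving HILT with exercise", and section 3.2.3 covers experiences "throughout the 12-week intervention involving HILT with exercise or placebo laser therapy with exercise".

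Eight sessions or weeks:

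- Executive Summary: "For eight consecutive weeks, both groups will receive their prescribed laser treatment".
- Section 1.1: "Each group is scheduled for weekly 60-minute sessions for eight weeks in consecutive weeks".
- Section 3.1.6, strengthening exercises: the last step of the progression is "Week 6-8: 2 sets, 10 repetitions, 10-second hold".
- Section 3.1.7 puts the end of treatment, and the assessment tied to it, at week 8.
- Section 3.3.4 (Table 3.0) funds participant travel for 8 sessions.

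The follow-up interval is consistent. The Executive Summary has "follow-up after three months of the last session", 3.1.7 also says three months, and 1.1 says 12 weeks. The trial week is not consistent: 3.1.7 heads the follow-up item as week 12 and then places it at week 24. Table 3.0 also puts the second X-ray at week 24.

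**The concern.** The number of sessions is the dose of the experimental treatment, and the protocol itself has to fix it. Section 3.1.6 is where a treating physiotherapist would look, and it disagrees with the summary, the introduction and the visit schedule. Twelve appears four times in three sections, so it is not a single slip.

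The conflict carries into the visits. Staff who give twelve sessions and book the first post-baseline visit at week 8 assess participants before treatment has ended, although that visit is defined by the end of treatment. Staff who give eight sessions and book follow-up at week 24 measure the long-term effect, a main objective in section 1.4.1, later than the stated three months. Both visits are levels of the time factor in the repeated-measures ANOVA of section 3.1.8, and the structural X-ray outcome depends on the second one.

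**Working it through.** **Inputs**

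- Sessions: 12 (3.1.6) or 8 (Executive Summary, 1.1, 3.1.7, 3.3.4), once a week.
- Energy per laser session: 3190 J (3.1.6).
- Follow-up interval: three months (Executive Summary, 3.1.7) or 12 weeks (1.1). Three calendar months are 365.25 / 4 / 7 = 13.04 weeks, so 12 to 13 weeks covers both.
- Stated visit weeks: 8 and 24 (3.1.7).
- Participant travel: RM10 per session, 40 participants (3.3.4).

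**Step 1: the plan's own figure.** RM10 × 8 × 40 = RM3,200, as budgeted. With RM800 for researchers this gives the RM4,000 travel line. The lines sum to 10,200 + 4,000 + 6,000 + 1,400 + 18,400 = RM40,000, the full grant. The budget was therefore built on eight sessions.

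**Step 2: visit weeks.** The last session falls in week s, where s is the number of sessions, and follow-up falls at week s + 12 to s + 13.

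| | 8 sessions | 12 sessions | Stated in 3.1.7 |
|---|---|---|---|
| Post-intervention visit | week 8 | week 12 | week 8 |
| Follow-up | week 20 to 21 | week 24 to 25 | week 24 |

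Eight fits only the first stated week and twelve only the second. Two mixed readings are possible:

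- Eight sessions with follow-up at week 24: lag 24 − 8 = 16 weeks, which is 3 to 4 weeks longer than stated.
- Twelve sessions with a visit at week 8: the visit comes after 8/12 = 67% of sessions.

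Reading the week-12 heading as 12 weeks after treatment is plausible. It does not help, because the same item still says week 24.

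**Step 3: dose.** 8 × 3190 = 25,520 J and 12 × 3190 = 38,280 J. The difference is 12,760 J, a ratio of 1.5.

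**Step 4: cost of twelve.** RM10 × 12 × 40 = RM4,800, which is RM1,600 above the budgeted amount. The total becomes RM41,600 against a grant of RM40,000. The extra sessions number 4 × 40 = 160.

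**The case against.** The strongest reply is that both visits are tied to treatment events: one follows the last session and the other comes three months later. Staff who work from those anchors would time both correctly under either count, so the fault is a wrong week label and not an undefined schedule. This holds as far as it goes, and it limits the timing harm to staff who follow the week numbers. It leaves the session count unsettled, and the labels remain in the same items as the anchors.

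Some of the support for eight is weaker than it looks. Section 3.1.6 offers the exercises as examples to be adapted to the patient, so a progression ending at week 8 corroborates eight without fixing it. The budget is mixed: it funds eight sessions but places the X-ray at week 24, which fits twelve. The case for eight rests mainly on the Executive Summary, 1.1 and 3.1.7.

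Section 3.1.6 also refers to an appendix for the laser details. That appendix and the trial flow chart could not be examined, so which count staff would follow in practice is uncertain. Neither could remove a contradiction in the written text.

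Finally, the joule totals are the session ratio in other units, and the protocol sets no limit or threshold on cumulative energy. The RM1,600 is administrative and arises only if twelve is chosen. Both remarks are fair; neither touches the contradiction.

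**Conclusion.** The concern holds, and the protocol must be corrected. It states two treatment durations, and the two visit weeks in 3.1.7 are mutually incompatible under either. At stake are a 50% difference in cumulative laser dose and one of two timing errors: a follow-up 16 weeks after treatment instead of 12 to 13, or a post-intervention visit after 67% of sessions. The comparison between arms is not biased, because both have the same stated count. The damage is to the dose delivered, the timing of both post-baseline assessments, and reproducibility.

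This assumes that sessions run weekly without gaps, so that the last one falls in the week equal to the session count, and that three months means 12 to 13 weeks.

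**What to change.** Adopt one session count throughout.

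**If eight, the better-supported choice:**

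- Change both arms in 3.1.6 to eight weekly sessions, and the intervention length in 3.2 and 3.2.3 to 8 weeks.
- Change week 24 to week 20 in 3.1.7 and in the X-ray line of 3.3.4. Week 20 is 12 weeks after the last session and agrees with the follow-up length in 1.1.
- Cost: protocol wording only.

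**If the investigators intend twelve:**

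- Move the post-intervention visit in 3.1.7 to week 12 and keep week 24.
- Extend the strengthening progression in 3.1.6 to week 12.
- Correct the Executive Summary and 1.1.
- Raise participant travel in 3.3.4 to RM4,800.
- Cost: RM1,600 from a source still to be named, and 160 more sessions in total.

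**Either way,** replace the week-12 heading of the follow-up item in 3.1.7 with wording that says 12 weeks after the last session. Check that the laser appendix and the flow chart show the same count.
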